### Allocation and blinding

The sample of OSPs will be randomly assigned to the control or the intervention groups with a 1:1:1:1 allocation. The randomization schedule will be computer-generated and stratified by service type (such as hospitals and optical shops). A stratified randomization is used to ensure that the four groups have a similar distribution in type as this characteristic may substantially affect the outcomes.

The allocation of OSPs will be conducted by a statistician otherwise not related to the research. Other than a code for each service provider and the service type, the statistician will have no other identifying information of the sampled participants.

After stratified random sampling, the allocation sequence will be generated by computer, and the randomization for each group will be initiated by the researcher. The USPs will be enrolled by the researcher and assigned randomly to the OSPs in each group. To balance confounding factor of individual USP, each USP will be assigned to four groups for equal visits.

The study subjects (OSPs) will be blinded to their allocation status as we have obtained a waiver for their informed consent. The USPs will not be blinded as they will need to implement BVIs according to the allocation status. The outcome assessors and data analysts will be blinded to reduce subjective analysis.

As no informed consent will be sought, unblinding on the side of OSPs is highly unlikely if possible at all. But if that occurs, a replacement of provider with similar characteristics will be identified for a replacement visit.

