**Fig. 1 Fig1:**
[figure not shown]
Flow chart of the study

The USPs must meet the following criteria to be eligible for the study: (1) people with refractive error profile of interest (myopia or myopia with astigmatism), and good ocular health; (2) fluent native speakers of the primary language of the district; (3) having a good memory. If the USPs meet any of the following criteria, they will not be eligible for the study: (1) having prior refractive eye surgery or had eye surgery within the last three months; (2) having manifest or intermittent strabismus, or amblyopia; (3) people with any ocular or health conditions that can cause variable spectacle prescription.

We will develop the sampling frame of all OSPs who meet our inclusion and exclusion criteria by crawling the data of Gaode Map, the leading map service App with the advantage of capturing both registered and non-registered optical shops in China. We will select the sample of OSPs with stratified and simple random sampling. Likewise, we will recruit USPs by posting part-time job announcements on campus posters and social media, like WeChat, and also through our existing USP network. The USPs will be paid for participation and reimbursed for other related expenses.

At recruitment, all USPs and their companions must sign the informed consent electronically through a web link sent by our emails. We have obtained a waiver for informed consent from the OSPs as the process may compromise the sample representation due to possible participant self-selection. We meet the criteria of consent waiver for the USP studies as stipulated by the medial ethics: (1) data analysis will only be performed at the aggregated level rather than targeting individual participants; (2) de-identification for the participating individuals and institutions will be fully implemented; and (3) services performed on USPs are not critical services where resources must be protected for the real patients [23].

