### Baseline refraction

Refraction of each USP will be conducted prior to the launch of the field visits by the skilled optometrist who will be recruited within each setting to conduct individual refraction. For example, the baseline refraction in Guangzhou will be conducted by experienced optometrists from Zhongshan Ophthalmic Center at Sun Yat-Sen University, the state key laboratory of ophthalmology. Each item of the expert prescription will be used as the “optimal spectacle prescription” (Table 1) for a given USP. The tolerance limits (Table 1) are developed from published studies [5, 25–27] and evaluated through experts’ consensus.

**Table 1 Tab1:** Criteria for optimal spectacle prescription

Component of spectacle prescription	Tolerance limits compared with baseline prescription
Spherical power	± 0.50DS
Cylindrical power	± 0.50DC
Cylindrical axis	
(if baseline cylinder power ≤ − 0.50DC) (if baseline >−0.50DC to ≤ − 1.50DC) (if baseline >−1.50DC)	± 7° ±5° ± 2°
Pupil distance	± 2 mm
Corrected visual acuity	± 0.1

DS = diopter sphere, DC = diopter cylinder

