## Discussion

This randomized controlled trial is designed to investigate the effect of BVI by USP on the quality of optometry service. The outcomes will include optometry accuracy, provider adherence to best practices in conducting optometry, and structural elements of the OSPs. The results of this study will not only provide valuable information on the quality of optometry service and identify a specific opportunity for quality improvement but also provide much-needed empirical evidence to aid policy-makers, education institutions and service providers on how to ensure that optical services provide quality eye care. The findings can be especially helpful for people with refractive error to obtain proper refraction and good service as BVIs can potentially be self-implemented by patients. The use of USPs in this study provides a reliable way of measuring and changing quality of the services.

Although we have waived informed consent for the OSPs, we will take strong measures to protect provider information. No service provider or practitioner identification details will be reported in publications or any other public spaces. There is also a way for USPs to prevent getting harm once their anonymity is exposed. All USPs will be intensively trained to present a letter with phone contact information from the university to explain their research roles in case of possible confrontation and also to avoid potentially harmful examination.

There are several limitations that should be considered. First, we will not be able to afford to buy spectacles due to limited budgets. So the results of the data can only reflect the provided optometry service quality, not the whole refractive error care. Second, we do not consider young children, only use adult USPs (aged 18 or up) in the study as mydriatic optometry is an invasive examination that cannot be ethically implemented in the USP study. Third, our USPs have real profiles of refractive error with various diopters, so different USPs may cause the individual difference. We will minimize the potential bias by assigning each USP to the four groups in addition to the random assignment of OSPs. Training will be provided to ensure each USP plays their roles consistently except BVI across groups.

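### Randomisation is stratified by service type but not by city, so the equal visits promised for each USP can probably be met only approximately

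*Protocol article*

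**What the plan says.** All of the allocation rules stand in the Protocol article, Allocation and blinding.

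- Stratification: "The randomization schedule will be computer-generated and stratified by service type (such as hospitals and optical shops". The bracketed words are examples of service type; city is not named.
- What the allocating statistician holds: "Other than a code for each service provider and the service type, the statistician will have no other identifying information of the sampled participants".
- How USPs are matched to OSPs: "The USPs will be enrolled by the researcher and assigned randomly to the OSPs in each group". USPs are therefore placed after the arms are formed.
- The balance promise: "To balance confounding factor of individual USP, each USP will be assigned to four groups for equal visits". The Discussion repeats the aim without the word equal: "We will minimize the potential bias by assigning each USP to the four groups in addition to the random assignment of OSPs".

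Three other sections suggest that USPs belong to a site. Study design and setting has OSPs sampled separately in each location, across Guangzhou and three cities in Inner Mongolia. Participants and recruitment requires USPs to be "fluent native speakers of the primary language of the district". Baseline refraction has each USP's reference prescription established "by the skilled optometrist who will be recruited within each setting". The article does not give the number of OSPs per city, the number of USPs, the visits per USP or the block size.

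**The concern.** Each OSP receives one visit. If every USP working in a city makes the same number of visits in each arm, the four arms must have equal totals in that city. A schedule that balances arms only within service type, over all cities together, does not produce this.

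Equal visits per USP matter because the USPs have different real refractive errors, and the Discussion offers assignment of each USP to all four groups as a protection against that. City is also plausibly prognostic. The protocol justifies stratifying by service type because it may substantially affect outcomes, and it describes Guangzhou as well developed and Inner Mongolia as relatively underdeveloped. The same reasoning applies to city, which would also carry the local USPs and the local reference optometrist.

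**Working it through.** **Inputs from the protocol.** 456 visits, 5% dropout, four equal arms, one visit per OSP, 44.1% versus 66.1% accuracy (Sample size calculation). The total reproduces: 456 / 0.95 = 480, and 480 / 4 = 120 per arm. The point changes none of these figures.

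**Assumptions.** The city split is not stated, so two are used: 120 in each city, and 240 in Guangzhou with 80 in each of the other three. Also assumed are one schedule pooled over cities and USPs who stay in one city.

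**Step 1. What equal visits require.** If USP *j* in a city makes k_j visits in every arm, each arm's total in that city is the sum of the k_j, the same for all four arms.

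**Step 2. Spread of an arm's count in a city of m OSPs.** With N = 480 and a quarter of OSPs in each arm,
SD = sqrt[ m × 1/4 × 3/4 × (N − m)/(N − 1) ].

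- m = 120: sqrt(22.5 × 360/479) = sqrt(16.91) = 4.11 around a mean of 30; 95% range 22 to 38.
- m = 240: sqrt(45 × 240/479) = sqrt(22.55) = 4.75 around 60.
- m = 80: sqrt(15 × 400/479) = sqrt(12.53) = 3.54 around 20.

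A simulation (10,000 runs) of exactly balanced allocation within two service-type strata, with a hospital share of 10% to 50%, gave the same SDs. Stratifying by service type does not restrain city.

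**Step 3. Gap between largest and smallest arm (same simulation).**

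| OSPs in city | Median gap | 95th percentile | Chance of four equal arms |
|---|---|---|---|
| 120 | 9 | 17 | about 0.1% |
| 240 | 11 | 20 | about 0.05-0.1% |
| 80 | 8 | 15 | about 0.1-0.2% |

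No run had equal arms in all four cities.

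**Step 4. Share of visits out of balance.** This is half the summed absolute deviation of the four arm counts from their mean, divided by m. Taking the mean absolute deviation as about 0.80 SD:

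- m = 120: 4 × 0.80 × 4.11 / 2 = 6.6 visits, 5.5%.
- m = 240: 4 × 0.80 × 4.75 / 2 = 7.6 visits, 3.2%.
- m = 80: 4 × 0.80 × 3.54 / 2 = 5.7 visits, 7.1%.

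The simulation agrees: about 5.5%, 3.2% and 7%.

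**Step 5. Effect on an unadjusted risk difference.** For two arms, the variance of the difference in city counts is (m/2) × (N − m)/(N − 1). Suppose accuracy in that city or region differs by 20 points from the rest (an assumption; the protocol gives no figure).

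- m = 120: 60 × 360/479 = 45.1; SD 6.72; as a share of 120, 0.056; × 20 = 1.1 points.
- m = 240: 120 × 240/479 = 60.1; SD 7.75; as a share of 120, 0.065; × 20 = 1.3 points.

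The corresponding 95% limits are about 2.2 and 2.5 points.

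**Step 6. Scale.** The planned effect is 22 points. The standard error of the risk difference at 120 per arm is sqrt[(0.441 × 0.559 + 0.661 × 0.339)/120] = 0.0626, or 6.3 points. The chance component is therefore about 3-4% of the variance (1.12²/6.26² = 3.2%; 1.29²/6.26² = 4.2%).

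**Step 7. With city in the stratification.** Permuted blocks of four keep arms within 1 of each other in each stratum. With two service types that is about 2 per city, against a median gap of 9 at 120 per city.

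**The case against.** The protocol never says that a USP stays in one city. The language criterion speaks of a district and the refraction section of a setting, so an Inner Mongolia USP might visit all three cities there. Nor does the article say that one schedule is pooled over cities; separate schedules by site could be described in a fuller protocol. Both points stand, and the conclusion is conditional on them. If USPs moved freely within Inner Mongolia, the constraint would shift to the region. With 240 OSPs in each region the median gap would be 11.

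A reader might go further in four ways that the documents do not support.

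- *The statistician is barred from using city.* The text excludes other identifying information. A city code need not identify a provider, and the provider code could already carry the site.
- *OSPs would have to be moved between arms.* USPs are assigned to OSPs after the arms exist, so near-equal visits can be arranged within the allocation as it falls.
- *The comparison is biased.* City imbalance under randomisation is chance. The ordinary unadjusted standard error already includes it, and type I error is not inflated. The Statistical analysis plan section also foresees a covariate-adjusted sensitivity analysis, although it does not name city or USP.
- *The plan claims to balance city or the reference optometrist.* It makes that claim for the individual USP only.

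It is also fair to say that exact equality is a strict standard. The proposed remedy does not guarantee it either, because incomplete blocks can remain.

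**Conclusion.** The stated stratification does not support the stated equal-visit rule. If one schedule is pooled over cities and USPs work within one city, unequal city-by-arm totals are almost certain and exact equality per USP fails. What is lost is limited: roughly 3-7% of visits are out of balance under the two assumed city splits, and near-equality remains within reach. The cost to inference is chance noise of about 1.1 to 1.3 points SD under an assumed 20-point difference in accuracy, small beside a planned 22 points and a standard error of about 6.3. This does not threaten the validity of the trial. It is a worthwhile correction because the remedy is nearly free and lets the protocol keep its promise to near-equality.

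**What to change.** - Stratify the allocation by city and service type (4 × 2 = 8 strata with two service types), using permuted blocks of four.
- Give the statistician a non-identifying city code alongside the provider code and service type.
- Within each city, assign USPs to OSPs in sets of one per arm.
- Include city and service type in the primary model.
- State visits per USP as equal or as near equal as stratum sizes allow, since incomplete blocks can still leave differences of about 2 per city.

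The cost is one extra code in the randomisation file and some incomplete blocks in small strata. City is already known from the sampling, N stays at 480, and no visits are added. If the schedule is already run separately by city, one sentence saying so would settle the allocation part.

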## Methods

### Study design and setting

The study is designed as a prospective, single-blind, multi-center, randomized controlled trial with four arms – three intervention groups versus a common control group of the participating optometry service providers (OSPs).

The study will be carried out in Guangzhou and Inner Mongolia, China. Guangzhou is the capital city of Guangdong Province, representing a well-developed metropolitan in the south of China. Inner Mongolia’s autonomous region has fewer medical resources, representing relatively underdeveloped land in China. We chose three cities in Inner Mongolia, which are Bayannur (west), Hohhot (central) and Xinganmeng (east). Optometry service providers (OSPs) are considered for inclusion if they meet the criteria defined below. In each location, we will draw a representative sample of eligible OSPs using stratified and simple random sampling.

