### Outcomes

The primary outcome is optometry accuracy, a dichotomous variable of spectacle prescription. The prescription of a specific USP visit will be considered “accurate” if all of its readings fall within the tolerance limits in Table 1 to the optimal spectacle prescription. Otherwise, they will be judged as inaccurate prescriptions.

We will also assess providers’ adherence to best practices in optometry services as the secondary outcomes, such as the percentage of guideline-recommended procedures performed. We developed the following technical process indicators based on the guideline recommendations [28]: whether practitioners perform subjective optometry, try on adjustments, check old glasses, etc., and whether the operation is standardized and completed. A technical quality assessment checklist will be developed, and the USP will complete this checklist right after each optical visit. In addition to those technical processes of optometry, we will also evaluate patient experience, cost and service time. The patient-centered eye care in optometry or ophthalmology will be assessed with a revised patient perspective patient-centeredness (PPPC-R) rating scale by USP [29, 30]. Table 2 summarizes all outcomes to be collected.

**Table 2 Tab2:** Outcomes and their definitions

Name	Definition	Nature	How it is assessed	By whom
optometry accuracy	whether it is optimally prescribed for spectacle	primary outcome	spectacle prescription	USP and companion
completion of process items	the percentage of recommended procedures performed	secondary outcome	quality checklist	USP and companion
patient experience score	whether it is patient-centered	secondary outcome	PPPC-R rating scale	USP
cost	optometry fees, prices of recommended lenses and frames	secondary outcome	data collection form	USP and companion
service time	optometry time and waiting time	secondary outcome	data collection form	USP and companion

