### Data collection and management

We will collect a variety of eye care quality information and other related explanatory variables. Donabedian’s classification of quality of care (structure, process and outcome) will be used for quality evaluation [31]. The quality of structure level includes: personnel qualification (whether the practitioner is qualified and professionally certified) and equipment layout (whether the facility’s hardware meet the requirements of optometry and whether its layout is appropriate), etc. This kind of information will be obtained from publicly available websites, promotional materials and USP on-site observations.

Almost all data will be collected through the USP visit to the OSPs. The USP will visit each provider along with a companion as “friend”. While the USP is under examination by the practitioner, the companion will observe the equipment environment and the optometry procedures. At the end of each visit, the USP will ask for a spectacle prescription. The USP and the companion will work together to complete the quality checklist and other data forms on the smartphone within 15 min of the end of the optometry service. We assure that all collected data will be securely stored and protected in accordance with relevant privacy regulations and guidelines.

All data collected will be entered into the Research Electronic Data Capture (REDCap) system by USP companions. REDCap is a free and powerful cloud-based tool for data collection, storage and management [32]. It will also track any changes to the data in an audit trail and be able to fully de-identify the data. REDCap has bank-level security features, and only the investigators involved in this study can access the data. All forms collected for this study, including the signed consent forms, will be stored on REDCap system safely and conveniently.

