### Role of implementation

The study will be coordinated between Southern Medical University and Inner Mongolia Medical University. Day-to-day support for the trial is provided by:

Principle investigator: lead the study design and supervise the conduct of the trial; revise the protocol and amendments; approve the final protocol.Executive Investigator: develop research proposal and protocol; select and recruit USPs; conduct sample randomization and allocation; advise on study design and statistical analyses.Data manager: organize data capturing system; safeguard data quality; perform statistical analyses.Study coordinator: register trial; train USPs; obtain informed consent; coordinate optical service visits; assess quality of the USP visit.Study optometrist: develop “optimal spectacle description”; help train USPs.

The study team meets every two weeks. There is no trial steering committee or stakeholder involvement group.

And monitoring of trial conduct will be performed continuously. As the study does not involve any medications or invasive examinations or treatment, we expect minimum harm to the participants. The USPs and their companions will also be encouraged to report any irregularities or concerns through a feedback system. Thus we do not create an independent data monitoring committee for this study.

Protocol modifications will be communicated to the relevant parties in the form of an amendment. In case amendments concern or affect USP participants in any way, they will be informed about the changes. If needed, additional consent will be requested and registered. Also, on-line trial registries will be updated accordingly.

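### The plan says outcome assessors are blinded, but the secondary outcomes are assessed by the unblinded USP or the USP–companion pair, and two sections name different people for allocation

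*Protocol article*

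**What the plan says.** On blinding, the Allocation and blinding section of the protocol article makes three statements. Providers do not know their allocation. For the patients, "The USPs will not be blinded as they will need to implement BVIs according to the allocation status". For everyone downstream, "The outcome assessors and data analysts will be blinded to reduce subjective analysis". The Study design and setting section calls the trial single-blind.

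On who assesses, Table 2 in the Outcomes section has a column for this. For the primary outcome the row ends "spectacle prescription USP and companion". The same pair is listed for process items, cost and service time, and the USP alone for the patient experience score. The text above the table says that "the USP will complete this checklist right after each optical visit". Data collection and management says that "The USP and the companion will work together to complete the quality checklist and other data forms", and that companions enter the data into REDCap.

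On allocation, the Allocation and blinding section says: "The allocation of OSPs will be conducted by a statistician otherwise not related to the research". It then adds that a researcher initiates the randomization for each group. The Role of implementation section lists, among the Executive Investigator's duties, to "conduct sample randomization and allocation". That role also recruits USPs and advises on the statistical analyses.

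**The concern.** A reader judges the risk of detection bias from the blinding statement. Here it promises masked assessment, yet the only assessors named are the person who delivers the intervention and that person's companion at the visit. This matters most where the assessor has discretion. The PPPC-R is a rating of how patient-centred the visit felt. The checklist asks whether steps were done and also whether they were done to standard. One of its items, subjective optometry, is the subject of the line that the same USP has just spoken in Group B. A difference between arms on these outcomes could partly reflect what the rater expected.

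The allocation conflict is a separate matter. Independence of the person who allocates is a stated design feature, and the role list gives the task to someone involved in recruiting USPs and advising on the analysis.

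**Working it through.** The point rests on comparing sections; the plan gives no figure to reproduce.

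**Step 1: is the USP blinded?** No, by the plan's own statement in Allocation and blinding.

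**Step 2: is the companion blinded?** The plan does not say. The Brief verbal interventions section has USP and companion trained together and always working together. Data collection and management places the companion at the visit, observing the procedures, and the line is spoken before the examination. Knowledge of the arm is an inference, but a firm one.

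**Step 3: who assesses each outcome (Table 2)?**

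| Outcome | Assessed by | Room for the rater's judgement |
|---|---|---|
| Optometry accuracy (primary) | USP and companion | Low: provider's written prescription, fixed limits in Table 1 |
| Process items | USP and companion | Some: step done or not, plus whether done to standard |
| Patient experience (PPPC-R) | USP | High: the USP's own rating |
| Cost | USP and companion | Low: fees and quoted prices |
| Service time | USP and companion | Some: recorded by people who know the arm |

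All five rows name only the USP or the USP and companion. None names a blinded assessor.

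**Step 4: does sharing USPs across arms solve it?** Each USP makes equal numbers of visits in the four groups. That balances a rater's constant leniency or strictness. It does not remove an expectation that differs by arm.

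**Step 5: is there a conflict on allocation?** Allocation and blinding names an unrelated statistician; Role of implementation names the Executive Investigator. *Sample randomization* in the second might mean drawing the sample of providers, but the words *and allocation* that follow it cannot. The two sections disagree.

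**Step 6: how much could rating bias matter?** The documents give no size for an expectation effect, so any figure is an assumption. With 120 per arm, the standard error of a standardised mean difference is √(2/120) = 0.129. If there were no true effect but ratings shifted by δ SD, the chance of a result significant in that direction at the plan's 0.05 threshold is P(Z > 1.96 − δ/0.129):

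- δ = 0.10: 0.10/0.129 = 0.77, chance about 12%
- δ = 0.25: 0.25/0.129 = 1.94, chance about 49%
- δ = 0.40: 0.40/0.129 = 3.10, chance about 87%

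The spread shows that the answer is set by the assumed shift. It illustrates sensitivity and is not evidence that such a shift will occur.

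**The case against.** The strongest reply is that the plan hides nothing. The sentence just before the blinding claim says that USPs are unblinded, and Table 2 says who rates what. On this view, *outcome assessors* is only a loose term for whoever classifies the prescriptions, and *USP and companion* against the primary outcome means who obtains the prescription. That reading is fair for the primary outcome, but it cannot cover the PPPC-R or the checklist, which nobody else is said to score.

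Safeguards also count. The checklist is to be tested for validity and reliability, two people complete it within 15 minutes, and visits are voice-recorded. These limit error, but none masks the arm, and the stated use of the recordings is to check script fidelity. Unblinded PPPC-R rating is inherent in the method; that is a reason to say so, not to claim blinding. The analyst half of the sentence is not contradicted anywhere and stands.

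Two stronger readings are tempting. A reader might infer that the primary result is compromised. The documents do not support that: the prescription is written by a provider who does not know the allocation, and the limits are fixed in advance. The missing name for the classification step may also be a detail that an article leaves to the full protocol.

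A reader might also infer that an involved allocator could choose USP–provider pairings or replacement providers. The plan assigns USPs to providers at random within each group, and nothing in it links replacements to whoever holds the allocation list. Providers are sampled from a map-based frame before allocation with consent waived, so the usual route for selective enrolment is largely absent. What remains is the contradiction over who allocates.

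**Conclusion.** The concern holds in a limited form. The claim of blinded outcome assessment is contradicted by the plan's own outcome table. It is untrue for the process checklist, the PPPC-R score and the recorded times; cost is also collected unblinded, though with little room for judgement. The primary outcome is at low risk. Allocation is assigned to two different roles, one independent and one not.

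Both are contradictions between sections of the article, not gaps that a fuller protocol or analysis plan would fill. The conclusion assumes that a companion trained with the USP and present at the visit knows the arm; the USP's status needs no assumption. No numerical size of bias is claimed, and the 12% to 87% range depends wholly on assumed shifts. The consequence is for what the checklist and PPPC-R differences can support, and for the accuracy of the blinding and allocation statements. The change should be made.

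**What to change.** 1. In Allocation and blinding, limit the statement to what is or can be masked: the providers, the data analysts, and the classification of each prescription as accurate or not. Have that classification derived by program against the Table 1 limits, with the arm code masked.
2. State that the checklist, PPPC-R, cost and service time are assessed unblinded, and carry that caveat into the interpretation of the checklist and PPPC-R differences. Bring the single-blind label into line with the restated text.
3. Assign sequence generation and allocation to the unrelated statistician only, and amend the Executive Investigator's duties in Role of implementation to match. Clarify what the researcher does when initiating the randomization.

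The cost is wording plus a short derivation program. The price in presentation is a less favourable blinding statement for the secondary outcomes. These changes do not blind the ratings; they make the plan describe them correctly.
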